### Study population and setting

Eligible paediatric patients (aged 0–17 years) with documented diagnoses of HD or ARM are invited to participate at the COCOE clinic, Montreal Children's Hospital. Prospective patients are identified through weekly reviews of colorectal clinic schedules.

Although HD and ARM are embryologically distinct conditions with different surgical approaches and long-term outcome profiles, both require lifelong multidisciplinary follow-up and are managed by the same specialist team at COCOE. Enrolling both conditions within a single registry infrastructure reflects this shared clinical pathway and the impracticality of maintaining two separate registries at a single centre. To respect these clinical and methodological distinctions, primary and multivariable analyses will be conducted separately for each disease cohort rather than pooled, with disease-specific instruments and predictors as detailed in the Statistical Analysis section.

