### Outcome measures

The primary outcome and its definition are described in detail below. Pre-specified secondary outcomes are presented in Table 2 below, each with its definition, instrument or data source, timing of ascertainment, and analytic role.

**Table 2 pone.0356813.t002:** Pre-specified primary and secondary outcomes.

Outcome	Definition	Instrument / Data Source	Timing of Ascertainment	Priority	Analytic Role
**Time to fecal continence**	First clinic visit (confirmed at subsequent visit) at which the participant meets social continence threshold: BCS criteria (ARM) or BFS ≥ 17 (HD), from date of definitive repair	BCS (ARM) [16] or BFS (HD) [17], parent/caregiver proxy to age 11; self-report from age 12	Annual visits from age 3	**PRIMARY**	Kaplan–Meier estimation; Cox proportional hazards regression; Fine-Gray model for competing risks; landmark analyses at ages 5 and 10
HD-associated enterocolitis (HAEC)	≥1 physician-confirmed episode meeting Ruttenstock criteria requiring medical treatment	Clinical record review; REDCap adverse event log	Each annual visit; first episode date recorded	Secondary 1	Cox regression / Fine-Gray competing risks; descriptive incidence rate
Reoperation rate	Any unplanned surgical return to the operating room following index repair	Operative report review; REDCap surgical procedure log	Cumulative from index repair; each annual visit	Secondary 2	Cox regression / Fine-Gray competing risks; cumulative incidence curve
Disease-specific quality of life	HAQL total score and subscale scores (age-appropriate version)	HAQL questionnaire, self- or proxy-report [18]	Ages 6, 10, and 14 years	Secondary 3	Linear mixed-effects model (repeated measures); descriptive means by group
Transition readiness	Transition Readiness Assessment Questionnaire	TRAQ [19], self-report	Ages 14 and 17 years	Secondary 4	Linear mixed-effects model; descriptive score trajectory
Loss to follow-up (LTFU)	No clinic encounter, survey, or successful contact for ≥18 months while under age 18 and not yet transitioned	REDCap contact log; clinic attendance record	Flagged at 18-month mark; reviewed at each annual analysis	Secondary 5	Logistic regression (ever-lost vs retained); descriptive LTFU rate

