The primary outcome is time to achievement of fecal continence from the date of definitive surgical repair, analysed as a time-to-event outcome. For participants with ARM, continence is assessed using the Baylor Continence Scale (BCS) [16], with social continence defined as no soiling episodes in the preceding 4 weeks per published BCS criteria, completed by the parent or caregiver proxy up to age 11 and by self-report from age 12. For participants with HD, continence is assessed using the Bowel Function Score (BFS) [17], with social continence defined as a BFS score ≥ 17, administered to the parent or caregiver proxy up to age 11 and by self-report from age 12. Both instruments are administered at every annual clinic visit beginning at age 3 years. The earliest clinically meaningful assessment for continence is age 3, consistent with normal developmental milestones for voluntary bowel control. Participants will be censored at age 18, death, transition to adult care, or loss to follow-up, whichever occurs first.

Pre-specified secondary outcomes, listed in priority order, are: (1) Hirschsprung-associated enterocolitis (HAEC), defined as at least one physician-confirmed episode meeting the Ruttenstock diagnostic criteria and requiring medical treatment, assessed at each annual visit [20]; (2) reoperation rate, defined as any unplanned surgical return to the operating room following index repair, assessed cumulatively; (3) disease-specific quality of life, measured using the HAQL [18] at ages 6, 10, and 14 years using age-appropriate versions; (4) transition readiness, assessed at ages 14 and 17 years using the validated Transition Readiness Assessment Questionnaire (TRAQ) [19], and (5) loss to follow-up rate, defined operationally in the Loss to Follow-Up section. Each secondary outcome will be reported descriptively and, where the events-per-variable threshold is met (see Sample Size section), included as an endpoint in pre-specified multivariable analyses with the analytic role specified in the Statistical Analysis section.

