### Sample size and expected enrolment

The registry is designed for indefinite, continuous enrollment. We distinguish two enrollment streams: incident cases (children newly diagnosed with HD or ARM presenting to COCOE, estimated at a minimum of 5 per month) and previous cases (patients previously diagnosed but lost to follow-up and re-engaged, estimated at approximately 3 per month). Combined, the registry aims to enroll approximately 96 participants per year. Based on a prevalent backlog of an estimated 150–200 patients currently followed at COCOE, total enrollment over 5 years is projected at 480–680 participants.

While no minimum sample size is required for registry operation, we provide a feasibility projection. Based on published ARM cohort data reporting approximately 24–30% achieving full fecal continence [14], and HD cohort data reporting approximately 39% achieving a BFS ≥ 17 by adolescence, we project a combined continence event rate of approximately 30–35% within the first 5 years of registry operation [21]. This corresponds to approximately 145–240 continence events across the projected 480–680 enrolees, supporting inclusion of up to 14–24 covariates in the primary Cox model at an events-per-variable (EPV) threshold of 10 [22]. Importantly, this time-to-event framing includes all enrolled participants regardless of age at enrollment, resolving the limitation of the age-5 cross-sectional design by allowing older prevalent cases to contribute person-time and events from their enrolment date. Pre-specified multivariable analyses will be triggered only once this EPV threshold is confirmed at interim review; otherwise analyses will be limited to descriptive and unadjusted comparisons.

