### Study timeline and milestones

The registry opened to enrollment on 3 ^rd^ November 2025 and enrollment is ongoing. Formal analyses have yet to be conducted at the time of publication. Below is outlined the Projected Milestones and Study Timeline.

Projected milestones and Study Timeline are as follows:

**Year 1:** incident enrollment fully operational and backlog enrollment at least 25% complete;

**Year 2:** first annual data quality audit completed and first descriptive summary manuscript submitted;

**Year 3:** first interim analysis of the primary outcome conducted for participants who have reached age 5, if the EPV threshold is met;

**Year 4 and 5:** comprehensive registry report including all pre-specified multivariable analyses submitted for publication.

Milestone dates will be updated in subsequent protocol versions as the registry matures. As the study is a longitudinal prospective study, intermittent analyses of the data will be conducted throughout the study duration as is outlined in the Projected Milestones above.

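### Time to continence runs from repair, but prevalent children enter at enrolment and no rule covers those already continent, so their events would be dated by enrolment rather than by attainment

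*Protocol article*

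**What the plan says.** Protocol article, Outcome measures, sets the origin: "The primary outcome is time to achievement of fecal continence from the date of definitive surgical repair, analysed as a time-to-event outcome". Table 2 in that section defines the event: "First clinic visit (confirmed at subsequent visit) at which the participant meets social continence threshold". The schedule is: "Both instruments are administered at every annual clinic visit beginning at age 3 years". Only right censoring is listed: "Participants will be censored at age 18, death, transition to adult care, or loss to follow-up, whichever occurs first".

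Study population and setting admits children whatever their continence status: "Eligible paediatric patients (aged 0–17 years) with documented diagnoses of HD or ARM are invited to participate". Sample size and expected enrolment adds that "this time-to-event framing includes all enrolled participants regardless of age at enrollment", and presents this as curing a weakness of an age-5 cross-sectional design by "allowing older prevalent cases to contribute person-time and events from their enrolment date".

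Statistical analysis (Objective 3) names Kaplan–Meier, Cox and Fine-Gray models by disease, plus the proportions continent by ages 5 and 10. It does not describe how a child who enters years after repair joins the risk set, or what happens to one who meets the threshold at the first registry assessment.

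Study timeline and milestones plans for Year 3 a "first interim analysis of the primary outcome conducted for participants who have reached age 5, if the EPV threshold is met".

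**The concern.** Children who enrol years after repair have lived through much of the period in which continence is gained, but the registry did not observe them then. Take a child repaired in infancy, continent since age 4 and enrolled at 14. The first registry visit meeting the threshold is at 14. The event is therefore recorded about 14 years after repair rather than about 4, and its date reflects when the child was recruited.

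This affects the primary Kaplan–Meier curves, the Cox coefficients and, if the same data rules are used for them, the age-5 and age-10 benchmarks. Any covariate related to age at enrolment would pick up part of the artefact. The event projection, and with it the number of covariates said to be supportable, is affected too.

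**Working it through.** **1. The plan's own figures reproduce.** Enrolment: (5 + 3) × 12 × 5 = 480, and 480 + 200 = 680. Events: 480 × 0.30 = 144 and 680 × 0.35 = 238, against the stated 145–240. Divided by 10 events per variable these give 14.4 and 23.8, against 14–24. The lower total of 480 leaves out the backlog; with a backlog of 150 it is 630.

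**2. Share of prevalent children.** Incident: 5 × 60 months = 300. Re-engaged: 3 × 60 = 180. Backlog: 150–200. Prevalent share: (180 + 150)/630 = 52% to (180 + 200)/680 = 56%. Without the backlog it is 180/480 = 38%.

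**3. Who supplies the events.** Assume incident cases enrol near birth, evenly at 60 a year. By year 5, 60 × 2 = 120 have reached age 3 and 60 × 1 = 60 have reached a confirming visit at age 4. At 30–35% that is 60 × 0.30 = 18 to 120 × 0.35 = 42 events. To reach the plan's total, 144 − 42 = 102 to 238 − 18 = 220 events must come from prevalent children. Applying the plan's rate to those children instead gives 330 × 0.30 = 99 to 380 × 0.35 = 133, still well above the incident contribution. The rate itself comes from published cumulative proportions continent (ARM 24–30%; HD 39% by adolescence). These count everyone continent by a given age, not those becoming continent after enrolment.

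**4. Simulated effect on the curve.** None of these inputs is in the protocol: 35% ever continent; age at continence 3 years plus an exponential with mean 3; entry age uniform 0–17; up to 5 years of follow-up; age used as the time axis, taken as close to time since repair because repair is early. The truth follows directly: by age 5, 0.35 × (1 − e^(−2/3)) = 17%; by age 10, 0.35 × (1 − e^(−7/3)) = 32%. Ranges are across separate runs that differ in follow-up and visit detail.

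| Construction | By age 5 | By age 10 |
|---|---|---|
| Truth | 17% | 32% |
| From repair, no delayed entry | 3–5% | 16–19% |
| Delayed entry, already-continent counted as events | 13–24% | 52–70% |
| Delayed entry, already-continent removed | 17% | 31–32% |

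In these runs about 70–85% of counted events preceded enrolment.

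**5. Sensitivity to the assumptions.**
- A version with 55% prevalent children, annual visits, confirmation at the next visit, 30% or 39% ever continent and mean onset 2 or 4 years after age 3 gave the same pattern. Truth by age 10 was 24–37%, no delayed entry 14–22%, and delayed entry with already-continent children counted 53–77%. Removing them recovered the truth to within about 1 percentage point.
- That recovery needs person-time to end at the last visit whose result can still be confirmed. When follow-up ran to the end of observation, the estimate stayed low (17% against 29% by age 10 with 30% ever continent and mean 2).
- With half the cohort incident and already-continent children enrolling at a quarter of the rate of others, counting them gave 18% and 43% against 17% and 32%, and 39% of events preceded enrolment.

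**6. Year 3 interim.** Enrolment opened on 3 November 2025, so a child enrolled as a newborn is at most 3 at Year 3 and cannot have a confirming annual visit at age 4.

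**The case against.** A reader might infer that the protocol decides to score already-continent children as new events. It does not say so. It is silent, and the scoring follows only from applying the event definition with no baseline rule.

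A reader might also infer immortal-time bias. The enrolment-date wording reads most naturally as delayed entry, under which time before enrolment is not counted, so that is the less likely reading. It remains open only because the repair origin and the enrolment entry are never reconciled.

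Risk-set coding is often left to an analysis plan, and Figure 1, said to carry the censoring definitions, was not available for this check. That limits certainty about what is specified elsewhere. But the article itself fixes the origin, the event and the inclusion of prevalent cases, and claims the combination resolves a problem.

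The sizes depend on assumptions, and the last sensitivity run shows a much smaller effect. A tertiary clinic enriched for complex cases may well enrol fewer continent children. The age-10 excess persisted in every run; the age-5 effect varied in direction and size. The protocol also does not say that the landmark proportions are read from the Kaplan–Meier curve.

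Finally, it is tempting to say that the Year 3 age-5 limit causes the problem and should simply be deleted. Deleting it would barely change who supplies confirmed events.

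The planned safeguards do not answer the core point. Inverse probability weighting addresses loss to follow-up and non-response rather than late entry; separate disease models carry the problem into each cohort; and a child enrolled at 14 has no registry assessment at age 5 or 10.

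**Conclusion.** The concern stands as a gap between origin, entry and event definition that can materially distort the primary result. Under delayed entry without a baseline rule, the later curve is biased upward; without delayed entry, continence at ages 5 and 10 is understated. The magnitudes are illustrative, while the direction at age 10 under each reading was the same in every run. The share of prevalent children follows from the protocol's own accrual figures. That most projected events come from them rests also on incident cases enrolling near birth. The matter should be settled before the first analysis of the primary outcome; the protocol states that no formal analysis has yet been done. The Year 3 age limit is a secondary inconsistency with the inclusion of participants of any age.

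**What to change.** Amend Outcome measures (Table 2 and the primary-outcome paragraph), Sample size and expected enrolment, and Statistical analysis (Objective 3):

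1. State that time runs from definitive repair with delayed entry (left truncation) at enrolment, and that person-time ends at the last visit whose result can still be confirmed.
2. State that children meeting the threshold at their first registry assessment are not incident events. Report them as baseline prevalence and exclude them from the incident risk set, or treat them as left-censored in an interval-censored model. Apply the same rule to the age-5 and age-10 proportions.
3. Add a sensitivity analysis restricted to incident cases.
4. Restate projected events and supportable covariates, per disease, from incident attainment only.

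In Study timeline and milestones, reconcile the Year 3 age-5 limit with the inclusion of all participants. That interim will rest on prevalent or later-diagnosed children either way, so it particularly needs rules 1 and 2.

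The cost is protocol wording and an entry time in the survival code. The real price is fewer countable events, and hence a later date at which the events-per-variable threshold releases the adjusted models.

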### Study timeline and milestones

The registry opened to enrollment on 3 ^rd^ November 2025 and enrollment is ongoing. Formal analyses have yet to be conducted at the time of publication. Below is outlined the Projected Milestones and Study Timeline.

Projected milestones and Study Timeline are as follows:

**Year 1:** incident enrollment fully operational and backlog enrollment at least 25% complete;

**Year 2:** first annual data quality audit completed and first descriptive summary manuscript submitted;

**Year 3:** first interim analysis of the primary outcome conducted for participants who have reached age 5, if the EPV threshold is met;

**Year 4 and 5:** comprehensive registry report including all pre-specified multivariable analyses submitted for publication.

Milestone dates will be updated in subsequent protocol versions as the registry matures. As the study is a longitudinal prospective study, intermittent analyses of the data will be conducted throughout the study duration as is outlined in the Projected Milestones above.

### Participant recruitment and consent

Written informed consent is obtained from parents or legally authorised representatives at enrollment. Age-appropriate assent is sought from all participants with developing decision-making capacity, consistent with TCPS2 Article 4.2 [23] and MUHC REB guidelines: verbal or picture-assisted assent is used for children aged approximately 7–12 years, and written assent is obtained from adolescents aged 13–17 years, consistent with the age of capacity for research participation under the Québec Civil Code [24]. Assent is documented in REDCap alongside the consent record.

Verbal consent is obtained where written consent is not feasible (e.g., telephone or virtual visits, or when translation is required) and is documented [23], with audio recording where permitted. Participation is entirely voluntary and has no bearing on the care received at Montreal Children's Hospital.

All registry data are de-identified: each participant is assigned a unique registry identifier, and names do not appear on any data collection forms. A master linking log is maintained separately on a password-protected encrypted drive accessible only to the PI. Data are not anonymised in the irreversible sense,  re-linkage to the participant remains possible during active follow-up for clinical and re-contact purposes. Full anonymisation, meaning permanent removal of all re-identification keys, will be applied only upon permanent withdrawal or at study closure.

When a participant turns 18 years of age, active data collection ceases. Data already collected will be retained in de-identified form pursuant to Section 12 of the Act Respecting the Protection of Personal Information in the Private Sector (Québec Law 25, as amended by Bill 64 [25]), which permits continued use of de-identified data for research purposes without renewed consent, subject to ongoing REB oversight (MUHC REB No. 2026–10997).

### Loss to Follow-Up

A participant will be considered lost to follow-up if there has been no clinic encounter, completed survey, or successful contact (by telephone, email, or mail) for 18 or more consecutive months in a participant aged under 18 years who has not yet transitioned to adult care or withdrawn from the registry.

When a participant misses a scheduled visit without prior notification, the research assistant will initiate a standardised re-contact sequence: (1) two phone call attempts within 2 weeks; (2) email or written letter within 4 weeks, if contact information is on file; and (3) two further phone call attempts at 3 months. If no successful contact is made after this full sequence, the participant will be flagged as lost to follow-up in REDCap with the date of last confirmed contact recorded. All contact attempts and outcomes will be logged prospectively.

Rates and timing will be reported descriptively at each annual analysis. In survival and longitudinal analyses, the loss will be treated as censoring at the date of last confirmed contact. The potential impact of informative (non-random) censoring will be examined using inverse probability weighting (IPW) as a sensitivity analysis [26,27]. Factors independently associated with the loss will be examined using logistic regression (ever-lost vs retained) as a secondary analysis, with candidate predictors pre-specified to include: diagnosis type, age at enrollment, sex, aganglionosis length or ARM Krickenbeck category, area-level deprivation quintile, and distance from COCOE.

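### Loss to follow-up is defined at 18 months without contact, but the re-contact procedure sets the same flag about 15 months after last contact, or sooner

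*Protocol article*

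**What the plan says.** The Loss to Follow-Up section opens with the definition. A participant is lost when there has been no visit, questionnaire or contact "for 18 or more consecutive months in a participant aged under 18 years who has not yet transitioned to adult care" and who has not withdrawn. Table 2, in the Outcome measures section, repeats it for Secondary outcome 5: "No clinic encounter, survey, or successful contact for ≥18 months while under age 18 and not yet transitioned". The timing column of that row reads "Flagged at 18-month mark; reviewed at each annual analysis".

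The second paragraph of the Loss to Follow-Up section describes outreach: "When a participant misses a scheduled visit without prior notification, the research assistant will initiate a standardised re-contact sequence". The steps are two calls within 2 weeks, an email or letter within 4 weeks if details are on file, and "two further phone call attempts at 3 months". It then states: "If no successful contact is made after this full sequence, the participant will be flagged as lost to follow-up in REDCap". The date of last confirmed contact is recorded with the flag.

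The status has two uses. It is the outcome of a logistic regression of ever-lost against retained participants, which serves the objective on factors behind loss. It is also a censoring reason for the primary outcome: "Participants will be censored at age 18, death, transition to adult care, or loss to follow-up, whichever occurs first". The Loss to Follow-Up section places that censoring at the last confirmed contact.

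**The concern.** The same named status is set by two rules with different clocks. One counts 18 months from last contact. The other counts about 3 months from a missed visit and does not ask when contact last occurred. No sentence makes the earlier flag provisional or says which rule prevails.

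If the REDCap flag is taken as the analysis variable, some children will count as ever-lost who do not meet the written definition. Because the outcome is *ever* lost, a later return does not undo this. The reported loss rate, the factors found to be associated with loss, and the model behind the inverse probability of censoring weights would then depend on which rule filled the field. The early rule also partly measures missed appointments, and the number of previously missed appointments is one of the predictors named for the weights.

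**Working it through.** The plan gives no figure to reproduce; the check is a timeline in months.

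**Inputs**
- Definition: 18 months from last contact (Loss to Follow-Up, first paragraph; Table 2).
- Sequence: starts at a missed visit, last step at 3 months (Loss to Follow-Up, second paragraph). The 3 months are read as counted from the missed visit, the natural reading, although the text does not anchor them.
- Visit interval: 12 months (annual visits, Outcome measures).
- Contact between visits is possible: a completed survey counts as contact, and surveys may be completed between encounters or sent electronically before the visit (Patient-reported outcomes; Survey administration and burden mitigation).

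**Formulas.** Put the last attended visit at month 0 and the missed visit at month 12. Let L be the month of last contact, from 0 to 11.
- Sequence flag: 12 + 3 = month 15.
- Time since last contact at the flag: 15 − L.
- 18-month rule met: month L + 18.
- Gap between the rules: (L + 18) − 15 = L + 3.

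| Last contact (month) | Sequence flag (month) | Months since contact at flag | 18-month rule met (month) | Gap (months) |
|---|---|---|---|---|
| 0 | 15 | 15 | 18 | 3 |
| 3 | 15 | 12 | 21 | 6 |
| 6 | 15 | 9 | 24 | 9 |
| 9 | 15 | 6 | 27 | 12 |
| 11 | 15 | 4 | 29 | 14 |

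With last contact at the previous visit, the rules coincide only if visits are 18 − 3 = 15 months apart, which is not the plan's schedule.

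**Effect by type of child**
- *Never returns, both time points passed:* lost under both rules and censored at the same last confirmed contact. No difference.
- *Resurfaces inside the gap:* ever-lost under the sequence rule, retained under the definition.
- *Still out of contact at a data cut inside the gap:* lost under the sequence rule, not yet lost under the definition.

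**The case against.** The strongest reply is that the plan has one definition and one stray operational sentence. The 18-month rule is the only statement of when a participant counts as lost, and Table 2 repeats it as both definition and flag time. Table 2 also names the contact log and clinic attendance record, not the flag, as the data source for Secondary outcome 5. All contact attempts are logged prospectively, so the 18-month status can be derived at analysis whatever the flag says. The early flag also reaches few children: only those who miss a visit without notice and are not reached by four calls (two plus two) or by an email or letter where details are on file.

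Most of this stands. It makes the error recoverable and shows which rule to keep. It does not remove the conflict, because the flagging sentence sets the loss status itself, without condition, and nothing says that the flag is to be ignored.

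A reader might infer more than the documents support:
- *That censoring dates in all survival analyses depend on the rule.* Censoring is at last confirmed contact, so for children who never return the date is unchanged.
- *That children with complex disease, seen more often, are flagged sooner, creating a false link between severity and loss.* The documents describe annual visits and give no more frequent schedule by severity.
- *That the loss rate is overstated by a known number of points.* No return rate is given, so any such figure would only restate an assumption.
- *That visits after a return are discarded, against the plan's expectation of re-engaged patients.* The text does not say so. The previous cases in the Sample size section are an enrolment stream, not participants returning after being flagged. How returners are handled is a separate question, equally open under the 18-month rule alone.

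**Conclusion.** The contradiction is real: it lies within the Loss to Follow-Up section, and Table 2 confirms it. With annual visits the early flag precedes the 18-month point by 3 months when last contact was the previous visit, and by up to 14 months in the cases tabulated. This rests on a 12-month interval and on counting the sequence from the missed visit; small shifts in either leave the conflict in place.

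The consequence is confined to children who resurface inside the gap and to data cuts that fall in it. For them the loss rate, the ever-lost regression and the censoring-weight model can differ. How many children this concerns cannot be determined from the documents.

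The severity is moderate. The affected outcome is last in the plan's priority order and the intended definition is stated twice. The source records allow correction, and the final censoring date of a child who never returns does not move. It still deserves correction now, because enrolment is open, no formal analysis has been done, and the status is both a pre-specified outcome and a censoring reason for the primary outcome.

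**What to change.** - In the second paragraph of the Loss to Follow-Up section, let a failed re-contact sequence set a separate interim status, for example *unreachable, under re-contact*.
- Assign the loss-to-follow-up status only when 18 months since last confirmed contact is reached, as Table 2 already has it.
- State that Secondary outcome 5, and loss as a censoring reason, are derived from the contact log and attendance record on that rule. This also covers a child for whom no missed visit ever started the sequence.
- As a related clarification, state whether a participant who returns after being classed as lost resumes follow-up in the survival analyses.

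The cost is one extra REDCap status value and a few sentences of protocol text. The downside is that the loss flag is set some months later than under the present outreach paragraph; the interim status keeps these children visible to the research assistant meanwhile.
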